### Sample size

This study employes a three-arm, parallel-group, randomized controlled design (1:1:1 allocation), with the MoCA score as the primary endpoint. One-way analysis of variance (ANOVA) is used to compare differences among the three groups. Due to the lack of a clear anticipated effect size, based on previous rTMS studies in PSCI (26–28), we adopt Cohen’s f ≈ 0.32 as the expected effect size. Using G*Power 3.1 (test type: one-way ANOVA; effect size *f* = 0.32; *α* = 0.05, two-tailed; power = 0.80), the estimated total sample size is 99 (33 per group) to detect significant differences in MoCA scores. To account for a potential 10% attrition rate, the final recruitment target is set at 105 participants (35 per group). Because *a priori* information on within-subject correlation and covariate R^2^ was unavailable, we used one-way ANOVA for conservative planning. The primary analysis will use longitudinal models with covariate adjustment, which is expected to provide equal or greater efficiency than the planning model.

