### Randomization and blinding

The allocation sequence is computer-generated by an independent statistician using block randomization (block size = 3) with a 1:1:1 ratio for the MAG, ACU, and SHM group. Allocation concealment is implemented using sequentially numbered, opaque, sealed envelopes. Each envelope contained an allocation card corresponding to the group assignment. Envelopes will be opened sequentially by treating physicians to deliver the allocated intervention.

Given the nature of the magnetic stimulation, acupuncture, and sham magnetic stimulation intervention therapies, it is not possible for the treating physicians to be blinded in this trial. However, participants, outcome assessors, and data analysts will be blinded to group allocation. To minimize bias, strict separation of roles is maintained between intervention operators, outcome assessors, and statisticians throughout the trial. Blinding assessment will be conducted after the final treatment session. All participants will be asked to guess their group allocation from four options: PC6 MAG, PC6 ACU, PC6 SHM, or uncertain. These responses will be used to calculate the James Blinding Index, which quantifies blinding success on a scale from 0 to 1, where 1 indicates complete blinding (all “do not know”), 0 indicates complete unblinding (all correct), and 0.5 represents random guessing (29). Given the potentially perceptible differences between active magnetic stimulation and sham stimulation, a higher risk of functional unblinding may exist between the MAG and SHM groups, which will be considered when interpreting the blinding assessment results.

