**Figure 2 fig2:**
[figure not shown]
Three specific intervention methods. **(A)**, PC6 magnetic stimulation; **(B)**, PC6 localization and acupuncture at PC6; **(C)**, PC6 sham magnetic stimulation.

Across all groups, high-frequency rTMS will be administered over the L-DLPFC concurrently with each session of the assigned intervention. This protocol is designed to reflect the “central regulation + peripheral input” rehabilitation model and to ensure ethical consistency across treatment arms. In addition, all patients will receive conventional rehabilitation delivered by a multidisciplinary team in accordance with the Adult Stroke Rehabilitation Guidelines (NICE NG236) (30). This includes physical therapy, occupational therapy, and speech and language therapy, provided for at least 3 h per day, on at least 5 days per week, tailored to individual goals and needs. Rehabilitation also encompasses swallowing assessment and management, prevention of complications, and support for cognitive, psychological, and functional recovery, as outlined in the guideline recommendations for comprehensive stroke rehabilitation. We will document the type, frequency, and duration of conventional rehabilitation received by each participant. If a specific intervention within conventional rehabilitation is likely to influence a patient’s cognitive level, the investigator will document its type, duration, and intensity in detail in the Case Report Form form. Therefore, we will systematically document lesion side (left/right) and key lesion features (e.g., location and volume where available).

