### Statistical analysis

#### Clinical data analysis

All analyses will be performed using SPSS 26.0 (IBM, Armonk, NY, USA) with two-tailed tests (*p* < 0.05). Quantitative data will be expressed as mean ± standard deviation. Within-group comparisons will use paired t-tests. Between-group comparisons will employ one-way ANOVA or nonparametric rank-sum tests (Kruskal-Wallis test), depending on data distribution. Count data will be presented as numbers (percentages), to be analyzed by *χ*^2^ tests, Fisher’s exact tests, or Ridit analysis. Repeated-measures ANOVA with Greenhouse–Geisser correction will be applied to evaluate longitudinal changes across timepoints. Both intention-to-treat (ITT) and per-protocol (PP) analyses will be conducted. In the ITT analysis, missing outcome data will be handled using multiple imputation under the assumption of missing at random. For the primary outcome (MoCA), we will report effect sizes and 95% confidence intervals for between-group differences in score changes. Clinical relevance will be interpreted using published MoCA change ranges and distribution-based benchmarks, rather than a prespecified minimal clinically important difference (MCID). Pearson’s or Spearman’s correlation coefficients (selected based on data distribution) will be calculated to examine associations between clinical scales and neuroimaging parameters. Covariates including age, sex, years of education, time from stroke onset to study enrollment, and a quantitative metric capturing the “dose” of conventional rehabilitation (derived from documented type, frequency, and duration), and lesion side (left/right) will be incorporated into a multivariate linear regression model evaluating the primary endpoint (change in MoCA score) and key secondary cognitive outcomes. Furthermore, to explore the potential modifying effect of lesion side on treatment response, we will conduct an exploratory analysis by adding a Group × Lesion Side interaction term to the primary multivariate model for the MoCA change score and key imaging outcomes. These interaction analyses will be explicitly labeled as exploratory, and their results will be interpreted cautiously due to the limited statistical power for detecting interaction effects.

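### A planned regression for MoCA change, called primary in the analysis section, adjusts for rehabilitation received after randomisation; if treatment changes that amount, the group estimate is biased

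*Protocol article*

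**What the plan says.** Under Clinical data analysis, a quantitative measure of "conventional rehabilitation (derived from documented type, frequency, and duration), and lesion side (left/right) will be incorporated into a multivariate linear regression model", alongside age, sex, education and time since stroke. The model is for "evaluating the primary endpoint (change in MoCA score) and key secondary cognitive outcomes". Two sentences later a lesion-side interaction is to be added "to the primary multivariate model for the MoCA change score and key imaging outcomes", so the section itself attaches the word primary to this regression. The Sample size section adds: "The primary analysis will use longitudinal models with covariate adjustment".

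The source of the dose measure is in Intervention and grouping, in the text after Figure 2: "We will document the type, frequency, and duration of conventional rehabilitation received by each participant". The same paragraph describes that therapy as "provided for at least 3 h per day, on at least 5 days per week, tailored to individual goals and needs". It also allows that some components may affect the outcome, in a sentence that begins "If a specific intervention within conventional rehabilitation is likely to influence a patient’s cognitive level".

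Nothing restricts the measure to planned or pre-randomisation therapy, and nothing labels this adjustment as supplementary.

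**The concern.** Age, sex, education, time from stroke to enrolment and lesion side are all settled before allocation. Rehabilitation received is not: it accumulates alongside the allocated treatment. Randomisation protects a covariate-adjusted comparison only when the allocated treatment cannot influence the covariates.

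Treatment could influence dose here. The plan itself treats daily function, anxiety, depression and sleep as outcomes of the trial, and each could affect how much therapy a patient tolerates or is offered. Two things can then go wrong:

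- If dose also affects cognition, which the protocol allows, adjustment removes the part of the effect that runs through dose.
- If dose shares an unmeasured cause with recovery, adjustment can create a difference between arms where none exists.

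The Discussion states the aim as the incremental effect of PC6 magnetic stimulation over sham, and the analysis section promises an intention-to-treat analysis. Both point to the total effect of allocation, which is what the dose-adjusted coefficient may fail to estimate.

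**Working it through.** **The plan's own figure first.** One-way ANOVA, three groups, f = 0.32, alpha 0.05, power 0.80, from the noncentral F distribution with noncentrality f²N. The smallest N is 98, or 99 with equal groups, and power at 99 is 0.808. The stated 99 reproduces. That calculation contains no covariates, so it does not depend on whether dose is in the model.

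**Model for the bias.** In SD units, with T = allocated arm (1 or 0), U = an unmeasured prognostic factor, D = rehabilitation dose, Y = MoCA change:

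- D = aT + cU + error
- Y = τT + gD + bU + error

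Here a is the shift in dose caused by treatment, c and b are the links of U with dose and with outcome, g is the effect of dose on outcome, and τ is the treatment effect not passing through dose. U and D have unit variance within arm.

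- Total effect of treatment = τ + ga.
- Regressing Y on T and D gives D the coefficient g + bc.
- Adjusted treatment coefficient = τ + ga − a(g + bc) = τ − abc.
- Shift from the total effect = **−a(g + bc)**.

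The documents give none of a, b, c, g or τ. All values below are assumptions.

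**No true treatment effect and no dose effect (τ = g = 0).** The shift reduces to −abc.

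- a = 0: shift 0, whatever b and c are.
- a = 0.3, b = c = 0.4: 0.3 × 0.4 × 0.4 = 0.048 SD in size.
- a = 0.5, b = c = 0.6: 0.5 × 0.6 × 0.6 = 0.18 SD in size.

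**Other scenarios**, by formula and by least squares on 2,000,000 simulated patients:

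| a | b | c | g | τ | Total effect | Adjusted (formula) | Adjusted (simulated) | Shift (formula) |
|---|---|---|---|---|---|---|---|---|
| 0 | 0.4 | 0.4 | 0.3 | 0.5 | 0.500 | 0.500 | 0.500 | 0 |
| 0.2 | 0 | 0 | 0.3 | 0.5 | 0.560 | 0.500 | 0.498 | −0.060 |
| 0.4 | 0 | 0 | 0.3 | 0.5 | 0.620 | 0.500 | 0.500 | −0.120 |
| 0.2 | 0.4 | 0.4 | 0.3 | 0.5 | 0.560 | 0.468 | 0.469 | −0.092 |
| 0.4 | 0.4 | 0.4 | 0.3 | 0.5 | 0.620 | 0.436 | 0.434 | −0.184 |
| −0.4 | 0.4 | 0.4 | 0.3 | 0.5 | 0.380 | 0.564 | 0.562 | +0.184 |
| 0.4 | 0.4 | 0.4 | 0 | 0 | 0 | −0.064 | −0.063 | −0.064 |

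In every scenario the estimate without D was within 0.002 SD of the total effect.

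**Scale.** With three arms, f = 0.32 implies a largest pairwise difference between 0.32 × 3/√2 = 0.68 SD (two arms equal) and 0.32 × √6 = 0.78 SD (one arm midway). The non-zero null-case values are therefore 0.048/0.78 = 6% to 0.18/0.68 = 27% of that difference. With a = 0 the figure is 0%.

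**The case against.** The best defence is that the plan contains other MoCA analyses. The same section lists one-way ANOVA or Kruskal-Wallis between groups and repeated-measures ANOVA, and the abstract names only repeated-measures ANOVA for comparing arms. None is described as adjusted for dose. The longitudinal model promised under Sample size does not mention dose either. A reader might infer that the trial's single primary test is contaminated. The document does not support that, because it does not settle which test is primary. What stands is that one regression carries the word primary and contains this covariate.

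Three further inferences go beyond the text:

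- **Unblinded staff set the dose.** The statement that "it is not possible for the treating physicians to be blinded in this trial" concerns those who open the envelopes and deliver the allocated intervention. Conventional rehabilitation comes from a multidisciplinary team. The document does not say that this team knows the arm, nor that it is blinded. The routes through patient response need no unblinding.
- **Patients who leave early have a low dose by construction.** That holds only for a cumulative total. The formula is not given, and a rate such as hours per week would behave differently.
- **The bias would manufacture a benefit.** With a, b and c all positive, it reduces the MAG versus SHM difference. A spurious gain needs, for example, treatment to lower dose. The direction cannot be known in advance.

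The time window of the measure is not written down either. That it falls after randomisation is a reading of therapy received alongside the allocated treatment, though the natural one.

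On size, all inputs are assumed, and nothing in the document supports a particular treatment-induced shift in dose. With 35 per arm the standard error of a pairwise difference is √(2/35) = 0.24 SD, so 0.18 SD is about 0.75 of a standard error. That tempers the concern, but a larger sample would not remove the bias. Wanting to account for unequal co-intervention is reasonable, and the fix keeps a place for it.

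**Conclusion.** Wrong as written; should be fixed. The plan prespecifies a covariate that is, on its natural reading, observed after randomisation, and puts it in the regression it calls primary for MoCA change and in those for key secondary cognitive outcomes. Since this is an affirmative choice, leaving detail to a fuller analysis plan does not answer it.

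The bias is conditional. It is zero if treatment does not change the dose received. Under no true effect it reaches about 0.18 SD in size at the top of the assumed range (dose shift 0.5 SD, both correlations 0.6). It can take either sign. The documents do not show that it will occur, and the ANOVAs as described are free of it.

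**What to change.** In Clinical data analysis, remove rehabilitation dose from the regressions for MoCA change and the key secondary cognitive outcomes, and adjust only for variables fixed before randomisation. The other listed covariates (age, sex, education, time from stroke to enrolment, lesion side) meet that condition. Report rehabilitation received by arm descriptively. If a dose-adjusted model is wanted, keep it as a labelled sensitivity analysis that does not carry the main conclusion.

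The cost is a change of wording. The sample size is unaffected, because the planning ANOVA has no covariates. The small downside is losing whatever precision dose would have added.

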**Methods:**

This three-arm randomized controlled trial will enroll 105 patients with PSCI, randomly allocated 1:1:1 to the MAG (*n* = 35), ACU (*n* = 35), and SHM (*n* = 35) groups. Interventions will be administered 5 times/week for 3 weeks. All groups will receive high-frequency rTMS over the L-DLPFC (10 Hz, 80% rest motor threshold). The primary outcome is the Montreal Cognitive Assessment (MoCA) change from baseline to week 3. Secondary outcomes include the Mini-Mental State Examination (MMSE), Modified Barthel Index (MBI), Hamilton Anxiety Rating Scale (HAMA), Hamilton Depression Rating Scale (HAMD), Pittsburgh Sleep Quality Index (PSQI), and adverse events. Functional magnetic resonance imaging (fMRI) and functional near-infrared spectroscopy (fNIRS) data will be acquired at baseline and post 3-week treatment. Clinical data will be analyzed via SPSS 26.0 using repeated measures analysis of variance (ANOVA) to compare intergroup changes in outcomes across time points. Neuroimaging data will be processed in MATLAB R2018a. Correlation analyses will assess associations between clinical scores and neuroimaging parameters.

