## Method and analysis

### Research design

The present study is a three-arm RCT. Eligible PSCI patients will be enrolled from the Inpatient Department and Outpatient Clinic of Rehabilitation Medicine, West China Hospital, Sichuan University. Participants will be randomized in a 1:1:1 ratio to three groups: PC6 Magnetic Stimulation (MAG), PC6 Acupuncture (ACU), and Sham Magnetic Stimulation at PC6 (SHM). All three groups will concurrently receive rTMS (targeting the L-DLPFC). The study flowchart is presented in Figure 1, and assessment time points are detailed in Table 1. Ethical approval was granted by the Ethics Committee of West China Hospital of Sichuan University on March 13, 2024 (Approval No.: 20240313). The trial is registered at the Chinese Clinical Trial Registry: https://www.chictr.org.cn/, Registration No.: ChiCTR2400090768.

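### The MoCA-change regression leaves out baseline MoCA, and two different analyses are called primary without saying which one decides the trial

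*Protocol article*

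**What the plan says.** The Abstract (Methods) fixes the endpoint: "The primary outcome is the Montreal Cognitive Assessment (MoCA) change from baseline to week 3". Table 1 schedules MoCA at baseline and at weeks 3, 8 and 12.

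On how the groups are to be compared, the article says four things:

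- **Sample size:** "The primary analysis will use longitudinal models with covariate adjustment, which is expected to provide equal or greater efficiency than the planning model". One-way ANOVA is described there as the planning method, chosen because no within-subject correlation or covariate R² was available.
- **Clinical data analysis, regression:** the six covariates named above "will be incorporated into a multivariate linear regression model evaluating the primary endpoint (change in MoCA score) and key secondary cognitive outcomes". When the exploratory Group × Lesion Side term is introduced a sentence later, this regression is referred to as the primary model.
- **Abstract (Methods):** clinical data are analysed "using repeated measures analysis of variance (ANOVA) to compare intergroup changes in outcomes across time points". The analysis section repeats this method with a Greenhouse-Geisser correction and names no covariates for it.
- **Clinical data analysis, general rule:** "Between-group comparisons will employ one-way ANOVA or nonparametric rank-sum tests (Kruskal-Wallis test), depending on data distribution".

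Baseline MoCA is not named as a covariate anywhere in the article.

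**The concern.** There are two separate problems.

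**Precision.** A regression of raw change without the baseline score fixes the baseline slope at 1. If the true slope is below 1, a chance baseline difference between arms carries into the estimated effect through regression to the mean. Over repeated randomisations this averages to zero, so the cost is a wider interval and less power, not bias. With 35 per arm that cost can be appreciable, and the variable that removes it is already collected.

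**Which result decides.** A longitudinal model and a regression of a single change score are different analyses, and both are called primary. The only longitudinal method that the analysis section describes for clinical outcomes is repeated-measures ANOVA without covariates, which is not the covariate-adjusted model promised under Sample size. A Group × Time test over all four MoCA visits also asks a different question: it has (4 − 1) × (3 − 1) = 6 numerator degrees of freedom and responds to differences at weeks 8 and 12, whereas the week-3 comparison of three arms has 2. If these tests disagree, nothing in the article says which one is the trial's answer.

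**Working it through.** **Inputs.** Three arms: "Participants will be randomized in a 1:1:1 ratio to three groups". Effect size f: "0.32 as the expected effect size". Alpha and power: "0.05, two-tailed; power = 0.80". Stated total 99, or 33 per arm. The correlation r is not given, so a range is shown. The article does not say whether f is on the scale of the week-3 score or of the change.

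**Step 1: the plan's own figure.** One-way ANOVA, noncentral F with λ = N f² and degrees of freedom 2 and N − 3. At N = 99, λ = 99 × 0.32² = 10.14 and power is 80.8%; at N = 96 it is 79.5%. The smallest total with equal arms is therefore 99, as stated.

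**Step 2: what baseline adjustment is worth.** With equal SD s at both visits, Var(change) = 2(1 − r)s². The residual variance given baseline is (1 − r²)s². The ratio is (1 − r²) / [2(1 − r)] = (1 + r)/2. The power column takes f = 0.32 on the change scale, so the adjusted f is 0.32/√((1 + r)/2), with one degree of freedom spent on baseline.

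| r | Variance ratio | Patients giving the precision of 99 | Power at 99: change → baseline-adjusted |
|---|---|---|---|
| 0.3 | 0.65 | 99 × 0.65 ≈ 64 | 80.8% → 94.6% |
| 0.5 | 0.75 | 99 × 0.75 ≈ 74 | 80.8% → 91.0% |
| 0.7 | 0.85 | 99 × 0.85 ≈ 84 | 80.8% → 87.0% |
| 0.9 | 0.95 | 99 × 0.95 ≈ 94 | 80.8% → 82.9% |

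These are upper bounds. Age and education are already in the model and explain part of baseline MoCA.

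**Step 3: the efficiency expectation.** If f = 0.32 is instead on the week-3 score SD, one-way ANOVA of that score has 80.8% power. Raw change has effective f = 0.32/√(2(1 − r)), and baseline adjustment has 0.32/√(1 − r²).

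- r = 0.4: change 0.32/√1.2 = 0.292, power 73%; baseline-adjusted 0.32/√0.84 = 0.349, power 87%.
- r = 0.5: change 0.32/√1 = 0.32, power 81%; baseline-adjusted 0.32/√0.75 = 0.370, power 91%.
- r = 0.6: change 0.32/√0.8 = 0.358, power 89%; baseline-adjusted 0.32/√0.64 = 0.40, power 95%.

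On this scale raw change does worse than the planning model when r is below 0.5 and better when it is above. The baseline-adjusted analysis does better at every r shown.

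**Step 4: error rate if the test can be chosen.** Null simulations used 4,000 trials at each r from 0.5 to 0.8, 33 per arm, four visits with equal correlation, and six covariates. The chance that at least one test reaches p < 0.05 was:

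- ANOVA of change, Kruskal-Wallis of change, Group × Time, and covariate regression of change: about 9.0-10.7%.
- The same without Kruskal-Wallis: 8.4-9.9%.
- Group × Time and the covariate regression only, standing in for the two analyses called primary: 7.6-8.6%.

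Each test alone stays at about 5%.

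**The case against.** Several stronger readings are tempting, and the article does not support them.

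- **That four analyses are each named as the main one.** Only two carry the label. One-way ANOVA is presented as a planning device; the ANOVA or Kruskal-Wallis sentence is a general rule that does not mention MoCA; and the Abstract applies repeated-measures ANOVA to outcomes in general. In the analysis section, the word primary may even serve only to distinguish the base regression from its interaction version. The conflict is therefore between two labelled analyses, with two more on offer.
- **That the efficiency statement is false.** It is worded as an expectation and concerns covariate-adjusted longitudinal models, not unadjusted change. Step 3 contradicts it only if f is on the week-3 score scale and r is below 0.5, and the article states neither. If f is on the change scale, analysis of change has the planned 80.8%.
- **That the omission biases the result or invalidates 99.** It does neither. A valid interval already allows for chance imbalance.
- **That the error rate doubles.** The highest figures in Step 4 count ANOVA and Kruskal-Wallis as two free chances, although the article makes them alternatives. The inflation arises only if the favourable result is put forward.

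It is also fair to say that the covariate list opens with a non-exclusive word, that a longitudinal model could use the baseline visit, and that an unseen analysis plan may set the order. These points lower the severity but do not remove the defect. An explicit six-item list that leaves out the outcome's own baseline is a poor specification, and two analyses called primary in one article contradict each other whatever another document adds.

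**Conclusion.** The point stands in limited form, as a should-fix. The change-score regression omits baseline MoCA and so gives up precision at any r below 1: at most 25% of the contrast variance at r = 0.5, 15% at r = 0.7 and 5% at r = 0.9. This assumes equal variances at the two visits, and the true gain is smaller to the extent that age and education already predict baseline MoCA. Separately, the article calls two different analyses primary and does not say which decides. Leading with the most favourable test would put the 5% error rate at roughly 8-10% under the simulated conditions. Whether the expected efficiency relative to the planning model is reached depends on the unstated r and the unstated scale of f. Baseline adjustment secures it, apart from a trivial loss of degrees of freedom.

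**What to change.** Name one primary analysis, and use the same name in the Abstract, Sample size and Clinical data analysis sections. Either of these would do:

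- ANCOVA of week-3 MoCA (or of MoCA change) on group, with baseline MoCA added to the prespecified covariates; or
- a baseline-adjusted longitudinal model with the week-3 group contrast as the primary estimate.

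Label repeated-measures ANOVA, one-way ANOVA and Kruskal-Wallis as supportive for MoCA, and do not let the observed distribution choose the primary test. Rehabilitation dose is measured after randomisation; if it is removed from the primary model for that reason, say so and give the reason.

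The cost is wording only. Baseline MoCA is already collected, and the sample size does not change. The choice should be fixed before unblinding, because a later one would not be credible.
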